### Intervention

Group A will participate in a before-school (7:30–8:15 a.m.), physical activity program for 12 weeks, 3 days a week (Tuesday, Wednesday, and Thursday). Children will be able to choose their preferred activity (including but not limited to walking, jogging, running, soccer, jump rope, and basketball). Each child will wear a Polar E600 heart rate monitor (chest strap and watch) during each activity session. We will ask each child to engage in moderate to vigorous physical activity with their heart rate ranging from approximately 120 beats per minute to 180 beats per minute. Each child will be provided a target heart rate based on their age before each session. All activity will be freely chosen by study participants while being encouraged to maintain an acceptable heart rate. Heart rate will be recorded and downloaded following each activity session. Study staff will also check and manually record each child’s heart rate a minimum of three times during each 45 minute session.

### Assessments

All participant baseline measures will be performed 1–2 weeks prior to the first physical activity session. Follow-up measures will be performed within 1 week following the final physical activity session. For both Group A and Group B, the testing and measurement sessions will be scheduled at a convenient time before or after school and will be performed in a private room at the school. At the two testing and measurement visits, study staff will obtain weight, height, waist, hip and neck circumferences, resting heart rate and blood pressure for each enrolled child. Children will be asked to complete several questionnaires at both baseline and follow-up regarding their physical activity, eating habits, feelings and emotions, and quality of life. These measurements and questionnaires are expected to take approximately 15–20 minutes. Parent(s) will also be asked to complete questionnaires before and after the physical activity program. The parent questionnaires will include information regarding their education level, their child’s physical activity, eating habits, medications, illnesses, family history and quality of life. These questionnaires will be directly mailed to the parents and will include a postage-paid return envelope. We will also be asking teachers of enrolled participants to complete a brief questionnaire regarding the child’s classroom behavior before and after the physical activity program.

### Measures

#### Anthropometrics

Each study participant’s weight will be measured using an electronically calibrated scale (seca 869 electronic personal scale, seca Ltd, Hamburg, Germany) in kilograms. The participant will wear only one layer of clothing and remove his or her shoes for the weight measure. The study participant will step on the scale, remain as still as possible, and the weight will be recorded as soon as the digital reading is constant. This process will be repeated two additional times and the average weight in kilograms of the 3 measures will be calculated and recorded on the data statistical form. Height will be measured without shoes using a transportable stadiometer (seca 213 Stadiometer, seca Ltd, Birmingham, UK) to the nearest 0.1 cm. Study participants will be asked to stand upright with their heels against the board while facing the study personnel performing the measurement. Height will be recorded on the data form. Using the participants’ height and weight, body mass index (BMI) will be calculated and recorded.

Waist, hip, and neck circumference will also be measured. Waist circumference will be measured at the level of the umbilicus to the nearest 0.1 cm. Hip circumference will be measured at the level of the greatest posterior protuberance of the buttocks. Neck circumference will be measured in the midway of the neck, between midcervical spine and midanterior neck, to within 1.0 mm. All circumference measures will be taken with the study participant standing upright and facing the study personnel performing the measurement.

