## Methods/Design

### Objectives

This study will aim to implement a 12- week before-school, physical activity program and examine the effect of this unstructured, moderate to vigorous, before-school physical activity program on academic performance, classroom behavior, emotions, and other health related measures. This study will take place at Malletts Bay School in Colchester, Vermont (VT), the 3rd largest community in the state of VT. Approval to conduct the study was received from the Colchester School Board as well as from the principal of Malletts Bay School. Malletts Bay is a public school servicing 3rd, 4th, and 5th graders with a total of 447 students (229 males, 218 females). Approximately 35% of these students are eligible and participate in the Free and Reduced Lunch Program. The proposed protocol was approved by the Institutional Review Board (IRB) of the University of Vermont.

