### Participants

Children from Malletts Bay School in grades 3rd, 4th, and 5th grade and ranging in age from 7 to 11 years will be recruited. An IRB approved consent form, group information form, as well as an introduction to the study letter will be sent home with each student. The letter will provide instructions as to how each interested student (along with a parent/legal guardian signature) should complete the consent form and group information form. Students will return their signed consent form along with a completed group information form to their teacher. Study staff will collect and review completed consent forms from the teachers.

Children will indicate on the group information form (included with the consent form) the group (A or B) they would like to participate (Table 1). The investigators will randomize the children to either Group A or Group B on a first-come, first-served basis. Once the maximum capacity for any one group (n = 50) is reached, children will be randomized to the other group if they have indicated their willingness to participate in the other group. Or if the preferred group is at maximum capacity and the child did not request to participate in the other group, then the child would be notified in writing that the requested group was no longer available.

**Table 1 T1:** Group Stratification

**Group A**	Week 0	Physical Activity Program	Week 12
	tests and measures	3 days/week	tests and measures
**Group B**	Week 0	No Physical Activity Program	Week 12
	tests and measures		tests and measures

Once the consent form is received by the study staff, children and parents will be notified through letters mailed to their home address as to what group their child will be participating. The parent(s) of the child will then be contacted by phone to schedule the first testing session.

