#### Data analysis

All statistical procedures will be performed in SPSS, version 18.0. Significance will be set at the 0.05 level. Descriptive statistics including means and standard deviations will be computed for all of the data. Differences among the groups at Week 0 and Week 12 will be assessed by using Student’s independent *t*-test. Furthermore to account for baseline differences, a general linear mixed-model analysis of variance will be performed. A power analysis was performed to determine the sample size needed to determine significant pre- and post-differences in each group. With the alpha level set at 0.05, an anticipated effect size of 0.8, and the statistical power level set at 0.8, the minimum total required sample size was 8 participants. A power analysis was performed to determine the sample size needed to determine significant differences between Group A and Group B with a one-tailed *t*-test. With the alpha level set at 0.05, an anticipated effect size of 0.8, and the statistical power level set at 0.8, the minimum total required sample size was 42, with a minimum sample size per group of 21 participants. Therefore, with the planned total of 100 participants in this study, 50 of which will be assigned to Group A and 50 assigned to Group B, the minimum sample size required for analyses will be achieved.

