## Discussion

The proposed study described in this paper is the first to the authors’ knowledge to examine the effect of an unstructured, moderate to vigorous, before-school physical activity program on academic performance, classroom behavior, emotions, and other health related measures in elementary school-aged children. The results of this study will provide evidence to support the feasibility and efficacy of an unstructured, moderate to vigorous, before-school physical activity program in children. The unstructured physical activity with limited equipment, yet moderate to vigorous intensity design would allow others to easily and affordably replicate. Often, the initiation of novel physical activity programs is often viewed as cost-prohibitive and labor intensive. The design, setting, and population, however, may be replicated in relatively any elementary school with limited supplies and with a limited budget. Furthermore, the proposed study will provide insight regarding the ideal physical activity intensity and duration necessary to achieve a positive increase in academic performance.

The current study allows the participants to select and/or indicate their preferred group- Group A, tests and measures with the physical activity intervention or Group B, tests and measures only. This randomization design may be considered a limitation of the study; however, differences within each group, treatment and control will be assessed in addition to comparisons between the two groups. These within-group analyses will allow evaluation of the outcomes attributable to the physical activity intervention rather than attitudinal variables that may have been introduced with the self-selection of the groups.

The findings of this study will provide valuable information for other research groups looking to increase physical activity levels of children via school-based interventions. Furthermore, it will ascertain whether an unstructured, moderate to vigorous, before-school physical activity program is an effective method for future large-scale implementation.

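### Raw BMI in self-chosen groups aged 7 to 11: the unadjusted Week 12 test carries any age or sex imbalance and within-group change contains growth, though the baseline-adjusted comparison with Group B is largely protected

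*Protocol article*

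**What the plan says.** **Measure.** The Anthropometrics section says that, from height and weight, "body mass index (BMI) will be calculated and recorded". No percentile, z-score or growth reference appears anywhere in the article.

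**Population.** Under Participants, children in grades 3 to 5 "ranging in age from 7 to 11 years will be recruited". The Objectives section gives the school roll as 229 boys and 218 girls.

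**Allocation.** Participants says "The investigators will randomize the children to either Group A or Group B on a first-come, first-served basis", but after each child has named a preferred group. The Discussion concedes this: "The current study allows the participants to select and/or indicate their preferred group". Nothing balances the groups on age or sex.

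**Analysis.** The Data analysis section states: "Differences among the groups at Week 0 and Week 12 will be assessed by using Student’s independent" t-test. It adds a general linear mixed-model analysis of variance to deal with baseline differences, and names neither age nor sex as a covariate.

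**Interpretation.** The Discussion offers the within-group analyses as the answer to self-selection, and says they allow outcomes to be credited to the activity program rather than to attitudes that go with choosing a group.

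**Standing of BMI.** BMI is not named as a main outcome. It belongs to the other health-related measures in the Objectives.

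**The concern.** Average BMI in this age range is taken to rise with age and to differ by sex. If children who choose the program are on average older or younger than those who choose testing only, or if the sex mix differs, raw BMI means will differ for that reason alone. An unadjusted test at Week 12 cannot separate this from a program effect.

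The second route is the within-group comparison. Baseline and follow-up lie about three months apart, and children grow in that time. A change within one group is the sum of growth and any program effect. The Discussion nevertheless treats such changes as evidence about the program. At stake is a wrong reading of BMI in either direction: a real reduction in Group A hidden by growth, or ordinary growth in Group B read as deterioration without the program.

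**Working it through.** The article gives no BMI mean, SD or growth rate, so it has no BMI figure to reproduce. Its one between-group sample-size figure does reproduce: effect size 0.8, one-tailed 0.05 and power 0.8 need 20.03 per group, rounded up to the stated 21 (42 in total). That figure does not bear on this point.

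**Inputs from the article**
- 50 children per group; significance level 0.05, taken here as two-sided.
- Baseline 1 to 2 weeks before the first session, a 12-week program, follow-up within 1 week after the last session. The interval is therefore 1 + 12 + 0 = 13 to 2 + 12 + 1 = 15 weeks.

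**Assumptions not in the article**
- Growth in BMI 0.3, 0.5 or 0.8 kg/m² per year.
- Between-child SD 3 kg/m²; SD of the individual change 0.5 or 0.7 kg/m².
- Half a year's difference in mean age between groups.
- No true program effect, except in step 3.

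**1. Unadjusted Week 12 t-test**

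Bias = growth per year × 0.5. Noncentrality = (bias / 3) × √(50/2), with 98 degrees of freedom.

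| Growth per year | Bias (kg/m²) | Bias in SD | Noncentrality | Rejection probability |
|---|---|---|---|---|
| 0.3 | 0.15 | 0.05 | 0.25 | 0.06 |
| 0.5 | 0.25 | 0.08 | 0.42 | 0.07 |
| 0.8 | 0.40 | 0.13 | 0.67 | 0.10 |

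No figure is offered for a sex imbalance, because nothing in the article gives its size.

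**2. Within-group change over 13 weeks (the short end of the interval)**

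Drift = growth per year × 13/52. Noncentrality = (drift / SD of change) × √50, with 49 degrees of freedom.

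| Growth per year | Drift (kg/m²) | Probability of a significant change, SD 0.5 | SD 0.7 |
|---|---|---|---|
| 0.3 | 0.075 | 0.18 | 0.12 |
| 0.5 | 0.125 | 0.41 | 0.24 |
| 0.8 | 0.20 | 0.79 | 0.51 |

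A longer interval would raise these slightly.

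**3. Masking in Group A**

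Take an assumed true reduction of 0.20 kg/m², growth of 0.125 and SD of change 0.5. The net change is 0.20 − 0.125 = 0.075. Noncentrality falls from (0.20/0.5) × √50 = 2.83 to (0.075/0.5) × √50 = 1.06, and power falls from 0.79 to 0.18.

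**4. Baseline-adjusted comparison with Group B**

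Growth common to both groups subtracts out; only a difference in growth rates remains. Take an assumed difference of 0.1 to 0.3 kg/m² per year over 14 weeks (the middle of the interval) and SD of change 0.4 to 0.8. The bias is 0.1 × 14/52 = 0.03 to 0.3 × 14/52 = 0.08 kg/m², and the rejection probability is 0.05 to 0.17.

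**5. Whether adding age and sex as covariates would help**

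A child's baseline age and sex are the same at both visits. As main effects they add the same term to the Week 0 and Week 12 values, so the term drops out of the child's change. With both visits observed, the time and group-by-time estimates do not move. A simulated data set confirmed this: both estimates agreed to rounding with and without the two main effects. They moved only when age and sex were also allowed to interact with time.

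**The case against.** The strongest objection is that this rests on an omission. The Anthropometrics sentence describes data collection and does not declare raw BMI the analysed endpoint. A condensed article may leave derived variables and covariates to a fuller plan. That stands as far as it goes: the absence of a z-score would be weak on its own. But the unadjusted Week 12 test and the attribution of within-group change are both written into the article, and both are unsafe for BMI as described.

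A reader might infer something stronger: that growth and imbalance will generally show up as program effects. The article does not support that, for three reasons.
- Group B is measured on the same schedule, so common growth cancels in the controlled comparison.
- The planned mixed model is there to account for baseline differences. Read as group by time, it removes a level difference due to age or sex and leaves only differing growth rates.
- If BMI rises with age, growth in Group A works against an apparent benefit. The 0.12 to 0.79 in step 2 is the chance of a significant rise, not of a false claim that the program lowered BMI.

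It is also fair to say that the root causes, self-selection and the Discussion's attribution claim, reach beyond BMI, and that BMI is one of many health measures. Both points limit the importance of the finding; neither removes it.

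**Conclusion.** The point holds in limited form and is a minor improvement. Two stated analyses are exposed. The unadjusted Week 12 test carries any age or sex imbalance, but a half-year age gap would move its error rate only from 0.05 to about 0.06 to 0.10. The within-group tests are more exposed: growth alone would give a significant change with probability 0.12 to 0.79, so they cannot bear the attribution the Discussion places on them. The baseline-adjusted comparison with Group B is affected only through differing growth rates.

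All sizes rest on assumed growth rates, SDs and an assumed age gap. The article does not show that the groups will differ in age or sex; it only leaves them free to. The direction of the within-group bias rests on the assumption that average BMI rises with age in this range.

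**What to change.** 1. Use BMI-for-age-and-sex z-scores for the group comparisons at Week 0 and Week 12.
2. Base BMI conclusions on the between-group difference in change (group by time). Enter age and sex with their time interactions, or as covariates in a baseline-adjusted model of the Week 12 value. Main effects alone in the repeated-measures model would change nothing.
3. Apply the same adjustment to waist, hip and neck circumference and to blood pressure.
4. Revise the Discussion so that within-group BMI change is described but not attributed to the program. Covariates do not remove growth from a within-group change; the comparison with Group B does.

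The cost is one derived variable, a few model terms and a few degrees of freedom. Beyond height and weight it needs only each child's age and sex. The downside is that z-scores compress at extreme BMI, so raw BMI can be kept for the change analysis. No sample size changes.

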#### Physiological measurements

Blood pressure and resting heart rate will be assessed with the BP760 Omron Blood Pressure Monitor with ComFit Cuff. The study participant will sit quietly for at least five minutes prior to the measurements to allow heart rate to reach a rested baseline. Two readings of both blood pressure and heart rate will be obtained and averaged. For blood pressure, if the two values differ by more than 5 mmHg, an additional reading will be obtained. A small cuff will be used for the children. The study participants will be instructed to abstain from heavy exercise for at least two hours prior their heart rate and blood pressure measures. Study participants will also be instructed not to ingest caffeine within 30 minutes before their resting heart rate and blood pressure measurements. The study participant will be comfortably seated, with the arm slightly flexed, palm up and the entire forearm supported at heart level on a smooth surface.

#### Academic performance

Academic performance will be assessed through several methods including grades, achievement test scores, and curriculum-based measures (progress monitoring). The curriculum-based measures are a unique method as these are sensitive to and are validated to monitor progress compared to curriculum-based assessments. Curriculum-based assessments are often lengthy, not administered on a regular basis, and compare student scores to national samples. Curriculum-based measures are easy to administer, can be given as often as wanted/needed, and provide immediate feedback. Progress monitoring with curriculum-based measures focuses on individualized decision making in general and special education with respect to academic skill development at the elementary grades. Progress monitoring can be conducted frequently and is designed to estimate rates of improvement [8].

The proposed study will be utilizing two curriculum based measures developed by Pearson based on the work by Fuchs and Fuchs. The first is the M-COMP, which measures progress in basic number operations (addition, subtraction, multiplication, division) through grade 8. The second measure is the Oral Fluency Measure which measures progress in comprehension, reading, vocabulary, phonics etc. Criterion and norm based reference points are available. The norms are established through an aggregate score of the students in U.S. using the Pearson measures [8]. The curriculum-based measures will be performed 1–2 weeks prior to the first physical activity session. Follow-up measures will be performed within 1 week following the final physical activity session.

### Questionnaires

#### Physical activity

Participants’ physical activity will be assessed with the Physical Activity Questionnaire for Older Children (PAQ-C) administered by the study staff [9,10]. The PAQ-C was developed and validated to compare and measure moderate to vigorous physical activity levels over a 7-day period among elementary school aged children.

#### Eating behavior

The University of California Cooperative Extension Food Behavior Checklist [11] will be administered to assess participant’s eating behavior. This validated 16-item food behavior checklist has an elementary reading level and includes six subscales -milk, fat/cholesterol, diet quality, food security, and fruit/vegetable.

#### Feelings and emotions

Feelings and emotions will be measured with the Positive and Negative Affect Scale, Child Version (PANAS-C) [12]. The PANAS-C was developed mainly as an instrument for use in a general school population as a brief measure of emotional experience that can be used to differentiate anxiety from depression in children. The PANAS-C is very simple (27 items) as children will be instructed to indicate how often they have felt a specific way (e.g., interested, sad etc.,) during the “past few weeks” with a 5-point Likert scale (1 = very slightly or not at all, 5 = extremely).

#### Health-related quality of life

Health-Related Quality of Life (HRQOL) will be assessed with the Pediatric Quality of Life Inventory (PedsQL) [13]. The PedsQL is a 23-item, reliable and valid tool for measuring HRQOL in children. The PedsQL is comprised of four multi-dimensional scales that include physical, emotional, social and school functioning which produce three summary scores of psychosocial health, physical health and a total scale score to measure HRQOL. The PedsQL instruments are sensitive to cognitive development and consist of developmentally appropriate forms along with a parent proxy-report for children ages 8–12 years [13].

#### Data analysis

All statistical procedures will be performed in SPSS, version 18.0. Significance will be set at the 0.05 level. Descriptive statistics including means and standard deviations will be computed for all of the data. Differences among the groups at Week 0 and Week 12 will be assessed by using Student’s independent *t*-test. Furthermore to account for baseline differences, a general linear mixed-model analysis of variance will be performed. A power analysis was performed to determine the sample size needed to determine significant pre- and post-differences in each group. With the alpha level set at 0.05, an anticipated effect size of 0.8, and the statistical power level set at 0.8, the minimum total required sample size was 8 participants. A power analysis was performed to determine the sample size needed to determine significant differences between Group A and Group B with a one-tailed *t*-test. With the alpha level set at 0.05, an anticipated effect size of 0.8, and the statistical power level set at 0.8, the minimum total required sample size was 42, with a minimum sample size per group of 21 participants. Therefore, with the planned total of 100 participants in this study, 50 of which will be assigned to Group A and 50 assigned to Group B, the minimum sample size required for analyses will be achieved.

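### The between-group t-test leaves out school grade and classroom teacher; with self-selected groups it may be confounded by grade mix, misstate its precision or lose precision

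*Protocol article*

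**What the plan says.** All references are to the protocol article.

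- **Data analysis, main comparison.** "Differences among the groups at Week 0 and Week 12 will be assessed by using Student’s independent" *t*-test. No outcome is treated differently, and "Significance will be set at the 0.05 level".
- **Data analysis, second comparison.** "Furthermore to account for baseline differences, a general linear mixed-model analysis of variance will be performed". Its fixed and random terms are not listed.
- **Data analysis, sample size.** The calculation targets "significant differences between Group A and Group B with a one-tailed" *t*-test: "an anticipated effect size of 0.8, and the statistical power level set at 0.8, the minimum total required sample size was 42", or 21 per group, against a planned 50 per group.
- **Participants.** Children come from grades 3, 4 and 5. Each states a preferred group, and places are filled in order of receipt up to 50 per group. Forms travel through the class: "Students will return their signed consent form along with a completed group information form to their teacher". No step balances the groups by class or grade.
- **Assessments.** "We will also be asking teachers of enrolled participants to complete a brief questionnaire regarding the child’s classroom behavior", before and after the program.
- **Academic performance.** "Academic performance will be assessed through several methods including grades, achievement test scores, and curriculum-based measures". Norms exist for the curriculum-based measures, but the text does not say whether raw or norm-referenced scores are analysed.

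Grade, teacher and classroom appear in no analysis and not in the sample size.

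**The concern.** Student's t-test treats the 100 children as independent and has no place for covariates. Two features of the design strain this.

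**Teacher.** One teacher may rate, grade and instruct several enrolled children. Their scores then share that teacher's leniency (behavior ratings, grades) or instruction (possibly M-COMP and Oral Fluency too). If the split between Groups A and B differs from class to class, part of the teacher effect enters the group difference, and the t-test's standard error does not count it.

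**Grade.** Arithmetic and reading can be expected to rise from grade 3 to grade 5. If the self-selected groups differ in grade mix, a raw comparison mixes grade with program. If the mixes are alike, grade only adds noise.

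Academic performance and classroom behavior are the first two outcomes in the stated objective, so the group conclusion on the main questions is at stake.

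**Working it through.** **1. The plan's own figure.** Inputs from Data analysis: d = 0.8, alpha 0.05 one-tailed, power 0.8. For two independent groups the noncentrality is d × √(n/2), with 2n − 2 degrees of freedom. At n = 21 this is 0.8 × √10.5 = 2.59 and power is 0.817; at n = 20 power is just under 0.80. The stated 21 per group (42 in total) is reproduced. It assumes independent children. At 50 per group the noncentrality is 0.8 × √25 = 4.0, and power is 0.99 one-tailed (0.98 two-tailed).

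**2. Teacher effect and type I error.** The document gives neither the number of teachers nor an intraclass correlation (ICC). Assumed: 100 children under 10 teachers (10 each) or 20 teachers (5 each), and ICC 0.05 to 0.20. Twenty classes fit the school's 447 pupils (447/20 ≈ 22 per class). Model with no program effect: score = teacher effect (variance ICC) + child error (variance 1 − ICC). A two-sided 5% t-test was simulated 4,000 times per setting; the Monte Carlo error near 5% is √(0.05 × 0.95/4000) = 0.3 percentage points.

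| How groups fall across teachers | True SE / t-test SE | Type I error |
|---|---|---|
| Evenly split within each teacher | 0.99 to 0.90 | 5% to 3% |
| Unrelated to teacher | 1.00 to 1.02 | about 5% |
| Uneven uptake (class share in Group A uniform on 0 to 1) | 1.04 to 1.25 | 5.4% to 11.1% |
| Whole classes in one group (not the stated design) | 1.11 to 1.68 | 7.5% to 23.6% |

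**3. Precision when uptake is unrelated to class.** The t-test is calibrated, but a model with a teacher term could remove the teacher variance. The t-test's standard error exceeds the attainable one by about 1/√(1 − ICC): 1/√0.95 = 1.03 to 1/√0.80 = 1.12.

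**4. Pre-post contrast.** Behavior and the curriculum measures are taken at both times, so a teacher effect that is constant over 12 weeks sits in both scores. Simulated with 20 classes of 5, ICC 0.1 to 0.3, an assumed pre-post correlation of 0.5 to 0.7, and class clustering of group choice with ICC 0.2 to 0.4 (the uniform case in step 2 corresponds to 1/(1 + 1 + 1) = 0.33):

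- raw Week 12 t-test: type I error 5.8% to 10.7%;
- regression on baseline: 4.9% to 6.9%;
- change scores: 4.6% to 5.5%.

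Teacher effects that shift between the two measurements would not cancel.

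**5. Grade.** *Confounding:* assume a 0.5 SD step per grade and grade mixes of 40/34/26% and 26/34/40%. With grades scored 0, 1, 2 the group means are 0.34 + 2 × 0.26 = 0.86 and 0.34 + 2 × 0.40 = 1.14. The spurious difference is 0.5 × 0.28 = 0.14 SD with no program effect.

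*Precision:* if grade is balanced and explains a share R² of the variance, a within-grade d of 0.8 becomes 0.8 × √(1 − R²). For R² of 10%, 30%, 50% and 70%, d is 0.76, 0.67, 0.57 and 0.44. One-tailed power at 50 per group is then 0.98, 0.95, 0.88 and 0.70.

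**The case against.** Four arguments stand against the point.

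- **Group is taken up child by child.** Returning forms through teachers is logistics, not evidence that uptake follows class lines. This stands. The usual cluster-trial inflation does not apply automatically, and with unrelated uptake the t-test keeps its 5% level. A reader might infer that the t-test's standard errors are simply wrong, or that false positives reach the 20% range. The documents do not support either: those rates need whole classes in one group, and an even split within classes makes the test conservative.
- **The plan also has a mixed model.** An article may leave its terms to a full analysis plan, so their absence is not a fault in itself. Baseline adjustment also removes much of any stable teacher or grade effect (step 4). This stands in part. The only stated purpose is baseline differences, the article does not say which analysis carries the conclusion, and the t-test is a stated choice.
- **Lost precision is not miscalibration, and power is ample.** Correct. The 3% to 12% in step 3 is recoverable precision. At d = 0.8 with 50 per group, power falls materially only if grade explains a large share of the variance.
- **The grade argument depends on the scoring.** Also correct: norm-referenced scores, if grade-specific, would weaken it. Similarly, teacher leniency bears on behavior ratings and grades; for M-COMP and Oral Fluency the case rests on grade level and shared instruction.

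Self-selection without balancing remains. Nothing in the enrolment process prevents uptake from differing by class or grade, and the t-test could not absorb it if it did.

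**Conclusion.** The point holds as a weakness in a stated method. The t-test omits two known factors related to the main outcomes, in a design where children choose their group. Three consequences are possible: confounding by grade mix, misstated precision if uptake follows class lines, and lost precision if it does not.

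Which applies, and how strongly, cannot be settled from the document. For ICC 0.05 to 0.20 and 10 or 20 teachers, all assumed, type I error of the raw Week 12 comparison is about 5% with unrelated uptake and about 5% to 11% with uneven uptake. It falls to near 5% where stable class effects cancel in a pre-post contrast. The 0.14 SD grade effect is an illustration, which baseline adjustment would reduce in part. The sample size figure is correct on its own terms.

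**What to change.** In Data analysis, for classroom behavior, grades, M-COMP and Oral Fluency:

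- add school grade (3, 4, 5) as a fixed effect and classroom teacher as a random intercept to the planned mixed model with baseline;
- base the group conclusion on that model and keep the t-tests as descriptive only.

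Teacher may be fitted as a fixed effect instead. If each teacher has a single grade, the teacher terms then absorb grade, and the cost is one degree of freedom per teacher less one (9 or 19 for 10 or 20 teachers). With a random intercept the cost is two degrees of freedom for grade and one variance component. The change is one line of text. Each child's grade and teacher are already known, so no new data are needed.
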